**Conclusions:**

This study may point to the need to use assessment methods that are convenient and efficient for older adult populations and that can be used as substitutes for in-person evaluations. Although it is a viable approach, expanding the sample size is essential to generate reliable normative data. This is an unprecedented area of research in the country and the Central American region.

**International Registered Report Identifier (IRRID):**

DERR1-10.2196/68520

## Introduction

### Background

Teleneuropsychology refers to the use of audiovisual technologies for remote neuropsychological assessments and interventions [1]. Specialty psychological services, namely, neuropsychological assessments, seek to integrate digital tools into conventional practice, combining traditional in-person measures for rich clinical observations with novel digital or remote assessments that allow for more precise quantification of behavioral patterns [2]. Teleneuropsychology requires the use of various tests and tools to evaluate a person’s current cognitive and emotional status. This service usually requires patients to visit assessment sites and undergo clinical interviews and neuropsychological testing. Nevertheless, health emergencies such as the COVID-19 pandemic hindered in-person visits, prompting mental health professionals to adopt remote evaluations or teleneuropsychological assessments as an alternate method. The Inter Organizational Practice Committee created new guidelines for the practice of teleneuropsychology during the pandemic [3,4] to aid with some of the difficulties that are common in teleneuropsychology, such as uncontrolled conditions of in-home assessments [5]. In Latin America, recommendations on the use of teleneuropsychology emerged during the pandemic, with a lack of normative data for various countries [3]. However, teleneuropsychology did not arise solely as a response to health emergencies. Before the COVID-19 pandemic, guidelines for remote testing had been created by the American Psychological Association and Joint Task Force for the Development of Teleneuropsychology Guidelines for Psychologists [6]. These guidelines were developed to address ethical and methodological challenges associated with internet-based assessments, such as limited confidentiality and security risks when using the internet. One key recommendation was to incorporate ethical limitations into the informed consent process, providing participants with a clear and thorough explanation of the unique aspects of teleneuropsychology assessments [7]. Moreover, historically, studies have explored the validity and feasibility of remote care, initially through telephone and later through videoconferences.

### Teleneuropsychology: How It Came to Be and Its Development Before the COVID-19 Pandemic

Teleneuropsychology’s origins date back to the 1980s, when telephones were used for patient follow-up and cognitive health assessments. By then, widespread telephone use in US households facilitated telephonic data collection, particularly in primary care for consultations and surveys. In the 1990s, telephones were used for follow-ups with patients and screenings to detect dementia in older adults [8] as they function as a cost-effective alternative to in-person surveys [9]. In this period, there was an initial exploration of the feasibility of videoconferencing for cognitive evaluations in older adults [10,11] and an ongoing development and validation of remote tests [12-21]. Telephone screening tools, such as the modified Telephone Interview for Cognitive Status (TICS-M) and the Mini-Mental Status Examination, offer benefits such as rapid administration and cost-effectiveness, making them suitable for large-scale epidemiological studies [22]. These tools can also help minimize dropout rates in longitudinal studies and overcome geographical barriers [23]. Older adults, who may have mobility issues or reduced motivation, often respond well to telephone assessments, enabling “cognitive triage” and follow-ups in hard-to-reach populations [24]. However, the effectiveness of telephone assessments largely depends on the design of the screening instruments [25]. In this context, videoconferencing presents several limitations, including the inability to assess praxis or visuospatial abilities [26], limited use of visual stimuli, and the examiner’s restricted ability to directly observe behavior in an uncontrolled environment [27]. In addition, communication challenges arising from hearing loss or cognitive decline further complicate the assessment process [28].

Since the early 21st century, research has explored the feasibility of teleneuropsychological assessments. Studies have shown no significant performance differences between videoconference and face-to-face assessments, demonstrating its feasibility and potential utility [27-31]. Furthermore, teleneuropsychology has not hindered clinical intervention or rapport building [29,30]. Diagnostic agreement between on-site and videoconference screenings for neurocognitive disorders has also been confirmed [32,33]. Likewise, teleneuropsychological assessments have shown to be feasible in different clinical settings, such as assessment of survivors of stroke [34]. Acceptability [35] and satisfaction [36] with teleneuropsychology have been documented, including assessments designed for use in Latin populations [37] and other underrepresented populations [38].

### State of Teleneuropsychology During COVID-19: Uses, Validation, and Research

Before the pandemic, a survey revealed that approximately one-fourth of professionals, primarily from the United States, used teleneuropsychology for clinical interviews and interventions [39]. This highlighted the underuse of teleneuropsychology, which was largely due to lack of reimbursement from Medicare and private insurance [40]. Challenges such as limited access to technology, inability to perform hands-on assessments, and reduced behavioral observation opportunities also hindered its adoption [41]. However, lockdowns increased the need for recommendations and research, leading to greater use of teleneuropsychology among practitioners [5,42-44]. Research during the COVID-19 pandemic underscored the necessity for further investigation into teleneuropsychology and its limitations. Individuals with lower incomes often lacked access to necessary technology [45,46]. In addition, participants’ computer literacy skills were frequently inadequate, and there was a scarcity of research on teleneuropsychology’s application in home health care [33,47-49].

Research in teleneuropsychology, especially concerning culturally diverse populations, has progressed following the declaration of the end of the COVID-19 pandemic [50-52]. Notably, neuropsychologists have reported significant use of this work method [53]. In addition, new tools such as the Tele-Global Examination of Mental State [54] and Tele Executive Function for children [55] have shown promising results.

Studies on validity have shown that standardized cognitive tests used in teleneuropsychology retain their psychometric properties and yield results comparable to in-person administration [56]. Similarly, research shows that teleneuropsychology assessments are reliable, as they often show stable results when repeated over time, indicating reliability in tracking cognitive performance [57]. In addition, remote assessments allow for broader participation while maintaining standardized administration protocols through platforms such as Zoom (Zoom Video Communications), REDCap (Research Electronic Data Capture; Vanderbilt University), and other secure testing software [5].

### Teleneuropsychology in Latin America: Research and Practice

Until 2021, no studies on teleneuropsychology had been reported in Latin America [41]. However, from 2021 to date, 8 studies have been documented regarding the use of teleneuropsychology in 4 countries in the region. Most of the studies are descriptive, and only 1 is a randomized controlled trial. In 38% of the studies, a satisfaction survey was included. In half of the studies, teleneuropsychology was used to evaluate participants, and in 1 study, telerehabilitation was performed. Results indicated good acceptance of teleneuropsychology as an assessment or rehabilitation modality by both participants and professionals [49,58,59]. Key benefits included reducing the stress of traveling to evaluation sites, increased accessibility to remote areas, increased comfort of home assessments [45,60], continued access during social distancing, and reduced COVID-19 risk [59]. Moreover, challenges noted by practitioners included patients’ unfamiliarity with technology; lack of environmental control; and insufficient access to technological resources, including internet connectivity [46].

These studies represent a significant initial progress in Latin America, revealing insights into the experiences of neuropsychology professionals in the region. Although Mexico and Argentina are middle-income countries, they face findings and challenges similar to those observed in high-income nations. Moreover, proposals for clinically applicable models are beginning to emerge in Latin America [61]. However, normative data in the region are scarce, a phenomenon not unique to the teleneuropsychology, and precedes the COVID-19 pandemic as a recurrent issue in Latin America clinical practice [62]. There is a pressing need for studies that test the feasibility of teleneuropsychology and contribute to the development of tools, models, and validations and the establishment of normative data for the diverse populations of the region.

The objective of this study is to conduct the first pilot study in Central America to assess the feasibility of a teleneuropsychology protocol and to generate normative data for a Panamanian sample. The specific objectives of the study are to (1) administer a teleneuropsychological assessment to a Panamanian sample of participants identified as having a low risk of developing dementia, (2) generate normative teleneuropsychological data from a Latin American sample in Panama to compare with a Hispanic sample in the United States, (3) compare performance on teleneuropsychological tests across different gender and age groups, and (4) assess the sample’s level of satisfaction with the administration of the teleneuropsychological evaluation battery using a standardized scale.

## Methods

### Participants

The protocol of this study is adapted from the Development and Validation of Teleneuropsychology Normative Data for Older Adults in Florida (FLOAT) [63], a study being conducted at the University of Florida with the aim of validating a battery in a healthy sample of older adults with low risk of developing Alzheimer disease and related dementias (ADRD). This study is cross-sectional, descriptive, and community based. As of November 11, 2024, we have recruited 67 (44%) out of 150 participants, all aged ≥50 years and residing in Panama. Details of participants invited to participate, recruited, and assessed are shown in Figure 1.

**Figure 1 figure1:**
[figure not shown]
Flowchart of participants included and excluded in the study. EDS: Escala de Satisfacción; TICS-M: modified Telephone Interview for Cognitive Status.

### Eligibility Criteria

Participant eligibility criteria are presented in Textbox 1.

Participant eligibility criteria.
**Inclusion criteria**
Are aged ≥50 years at the time of enrollmentHave a basic understanding and control of technological devicesHave access to a phone, tablet, or computerHave signed informed consentAre available to assist to all the program visits included in the studyHas no cognitive impairment at the time of enrollmentHas no conditions that limit or prevent them from completing the neuropsychological evaluation (ie, blindness, analphabetism, and severe physical limitations)
**Exclusion criteria**
A diagnosis of Alzheimer disease and related dementias or other neurological disorders that affect cognitive functioningA history or diagnosis of a severe psychiatric disease (ie, schizophrenia)Evidence of cognitive impairment (modified Telephone Interview for Cognitive Status <31)No access to internetLack of access to a smartphone with a webcam for videoconferenceOngoing participation in another clinical study or the intention to participate in another study

### Recruitment

Potential participants are recruited from the community in Panama through social media advertisements, flyers in community centers, and newspaper announcements. Individuals living outside the city are also encouraged to participate due to the availability of remote testing. The research team, which includes the principal investigator, research assistants, and trained psychology students, supervised by senior scientists, assist in recruitment and data collection. Participant recruitment process is displayed in Figure 2.

**Figure 2 figure2:**
[figure not shown]
Flowchart of the recruitment process. TICS-M: modified Telephone Interview for Cognitive Status; NACC: National Alzheimer’s Coordinating Center.

### Procedure

Participants undergo an initial screening to determine their eligibility. Those who meet the inclusion criteria and agree to participate will provide telephone-informed consent. Following this, participants complete 2 questionnaires: an adapted Spanish version of the modified TICS-M and the National Alzheimer’s Coordinating Center (NACC) Health Questionnaire. These assessments help identify any underlying neurological diseases or uncontrolled medical conditions that may impact cognition, such as depression or bipolar disorder. The screening aims to (1) confirm that the participant does not have cognitive impairment (eg, mild cognitive impairment or dementia) and (2) ensure that they have the cognitive capacity to provide informed consent. Participants scoring ≤31 points in TICS-M, indicating mild cognitive impairment or dementia, are excluded from the study. Those who do not meet the eligibility criteria are thanked for their time, and the assessment is discontinued.

Eligible participants receive a link to complete the questionnaires and surveys via email using the REDCap platform, an online platform designed for data collection and storage [64]. This process takes approximately 30 minutes. Later, a member of the research team schedules a 2-hour block for the teleneuropsychological assessment with ≥1 breaks if requested by the participants. A team member assists participants in setting up the videoconferencing technology. Before beginning the study, research staff reviews the informed consent document with the participant and addresses any questions.

REDCap is used to capture and store participant data, while Zoom facilitates the administration of neurocognitive tests. The screen-sharing feature is used to display test stimuli. For tasks requiring a scored motor component (eg, figure drawing), participants are asked to hold their drawings up to the camera, and a screenshot is taken for later scoring. These screenshots do not include any identifying information about the participants. Captured images are stored in the participant’s REDCap dataset for future analysis. During the assessment, 2 computers are used: a laptop and a touchscreen device, both of which project visual stimuli via the screen-sharing function. These stimuli are displayed in PowerPoint, and data collection is conducted in REDCap throughout the assessment.

### Measures

#### Overview

Following the FLOAT protocol, this study uses an open-access battery in Spanish that is part of the Uniform Data Set version 3 (UDSv3), comprising longitudinal data collected since 2005 at the National Institute of Aging funded Alzheimer’s Disease Research Centers (NACC, 2023). All measures in this study have been adapted for use with REDCap. In addition, several questionnaires, including the Health History, Functional Activity Index, Geriatric Depression Scale (GDS), and Demographic Information, have been modified to be completed directly by participants.

The evaluation process lasts approximately 3 hours, which includes 30 minutes for informed consent and screening measures, 30 minutes for participant-completed questionnaires via the REDCap platform, and approximately 2 hours for teleneuropsychological testing.

#### Screening Measures

The TICS-M [65] is administered in a Spanish version to screen for mild cognitive impairment. TICS-M measures domains such as orientation, verbal memory, attention, working memory, or abstraction and has no visual stimuli. Cognitive impairment is established at ≤31 points. This cutoff was used to determine which individuals could participate. Certain items have been modified to better suit the Panamanian context, such as replacing the question “Who is the president of the United States?” with “Who is the president of Panama?” In addition, the NACC Health History [66] measure is used to evaluate the participant’s general health history, helping to identify potential neurodegenerative diseases or other risk factors that may disqualify them from participation in the research.

#### Questionnaires

These questionnaires were obtained in the Spanish versions. Participants fill out these questionnaires online using a REDCap link provided by the study team.

The NACC-Demographics questionnaire [66] has been adapted to better suit the Panamanian population by modifying relevant questions and removing those that are not applicable, such as enquiries about the last digits of the zip code or the Alzheimer’s Disease Research Center. To assess symptoms of depression, the Spanish version of the GDS [67] is included, consisting of 30 yes or no questions completed via a REDCap form. If a participant scores >20 on the GDS, the study team contacts them to enquire about suicidal ideation. The Functional Activity Index [66] is used to evaluate an individual’s ability to perform daily activities, which may decline due to neurodegenerative processes. In addition, the Teleneuropsychological Assessment Satisfaction Scale provides participants with an opportunity to give feedback on various aspects of the assessment, including satisfaction, the use of Zoom and REDCap, instructions, advantages, difficulties, recommendations, and overall time.

#### Teleneuropsychological Tests

A variety of cognitive assessments are used to evaluate different cognitive domains. The Montreal Cognitive Assessment [68] is administered in an adapted Spanish version, serving as a cognitive screening tool that measures visuospatial skills, naming, verbal memory, working memory, attention, language, abstraction, and orientation. Verbal memory is further assessed using the Craft Story test [69], in which participants listen to a semantically related story and recall it both immediately and after a 20-minute interval, aiming to maintain the original phrasing. Similarly, the Rey Verbal Learning Test [70] requires participants to learn a list of 15 words through repeated exposure. After 5 trials, an interference list is introduced, and after a 20- to 30-minute delay, participants attempt to recall the original list, evaluating both immediate and delayed memory recall, as well as word recognition.

Visual memory and visuoconstruction skills are measured through the Benson Complex Figure test [71], where participants first copy a complex figure and then recall and recognize it after 10 minutes. Naming ability is assessed using the Multilingual Naming Test [72], in which participants observe and name figures, receiving semantic or phonemic cues if needed. The Digit Span Test [73] evaluates attention and working memory by having participants repeat a sequence of numbers in both forward and backward order, with increasing difficulty. Verbal phonological fluency [74] is assessed through a task where participants must generate as many words as possible starting with a given letter within a set time (excluding names, numbers, or repeated words). In the semantic fluency task [74], participants generate words belonging to a specific category, such as animals, vegetables, or fruits.

Executive function is measured using the Wisconsin Card Sorting Test-64 [75], a computer-based assessment where participants match cards according to rules they must infer, with alternative verbal response options available if they cannot control the screen. In addition, the Oral Trail Making Test is also used to measure executive functions. Divided in part A and part B, participants are first asked to count from 1 to 25 as fast as they can (part A). Later, they are requested to alternate between numbers and letters from 1 to 13 (part B). On both occasions, the time to finish, errors, and correct answers are recorded [76].

The Boston Naming Test [77], using a 15-item version from the Mayo Older Americans Normative Studies, presents participants with images to name, offering semantic or phonemic cues if necessary. Speeded information processing is evaluated using the oral version of the Symbol Digit Modality Test [78], in which a PowerPoint slide is displayed while responses are recorded in REDCap. Finally, premorbid intelligence is assessed with the Word Accentuation Test Chicago [79], where participants read a list of words and attempt to place the correct accentuation.

### Statistical Analyses

Neuropsychological test results will be analyzed using multivariate statistical methods. We will perform initial data analyses with chi-square and ANOVA tests to observe distribution across age groups or other groups of interest. We will obtain raw scores of each test as well as composites of cognitive domains to conduct further analyses per test and per cognitive domain. Comparisons will be made regarding sex and age groups. Student *t* test will be applied to examine differences in performance between sexes and within age groups (the sample will be divided in 3 groups: aged 51-59 years, 60-69 years, and >70 years). Multivariable regression analyses will be performed to assess linear relationships between age, years of education, or other (ie, income) variables and cognition. Once we have assessed and ruled out potential interaction effects influencing participant performance, we will proceed with an in-depth analysis of normative data stratified by age, sex, and education level. Test scores will be standardized into *z* scores based on the mean and SD of the respective group, and these *z* scores will be subsequently converted into normative scores for each assessment. Cases with incomplete data will be excluded from analyses via listwise deletion.

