**Methods:**

This is a cross-sectional, descriptive, community-based study derived from the Development and Validation of Teleneuropsychology Normative Data for Older Adults in Florida (FLOAT) study. The study’s final sample will include 150 participants (aged ≥50 years). Participants will undergo initial screening to determine their eligibility and will be included if they have a basic understanding of and access to technological devices such as telephones, tablets, or computers; are free of cognitive impairment or serious health conditions; and provide informed consent. Participants will complete 2 questionnaires to determine if they can continue in the study. Participants who are eligible will be assessed with a teleneuropsychology cognitive battery and will answer questionnaires via a REDCap (Research Electronic Data Capture) link.

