**Results:**

Feasibility will be assessed based on an analysis of the tools, funding, expertise, and resources needed to conduct neuropsychological assessments. So far, the study has proven feasible as researchers have been able to obtain a REDCap license and all other material necessary to carry out assessments. As of November 11, 2024, a total of 67 participants aged ≥50 (mean 62.2, SD 7.6) years had been assessed with questionnaires and a complete cognitive test battery. Sociodemographic and clinical characteristics show that participants on average had 16.7 (SD 1.9) years of formal education. A satisfaction questionnaire revealed that most participants were satisfied (22/67, 33%) or very satisfied (39/67, 58%) with the teleneuropsychological assessment, and most participants (58/67, 86%) would recommend this study to others. We expect to assess a similar number of women and men as well as different age groups with the teleneuropsychology battery. We plan to generate normative data for Panamanian adults aged >50 years.

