## Results

### Preliminary General Characteristics of the Sample

The demographic and clinical characteristics of the sample are summarized in Tables 1 and 2. Participants were mostly female (53/67, 79%) and were on average aged 62.2 (SD 7.6) years. Participants on average had 16.7 (SD 1.9) years of formal education. Most participants have a partner (44/67, 66%). Participants reported few cardiovascular, cerebrovascular, and psychiatric illnesses. Nevertheless, the most common chronic illness is hypertension (22/67, 33%), followed by hypercholesterolemia (19/67, 28%). Most participants identify as White (31/67, 46%) or other (20/67, 30%). Participants showed a high degree of functional independence in performing basic and instrumental activities of daily living. On average, participants had 1.5 (SD 1.8) symptoms of depression.

**Table 1 table1:** Protocol measures for teleneuropsychology assessment.

Measure			Description

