### Expected Outcomes for Creating Normative Data

In line with the FLOAT study [63], percentile ranks for each test’s raw scores will be calculated from cumulative frequency distributions and then normalized to a distribution with a mean of 10 and an SD of 3 (ie, scaled scores). These normalized scores will then be entered into a stepwise regression, including sex (male and female), education, and different age groups. Predictors contributing <5% of additional variance in the normalized scores will be retained for further regression-based adjustments.

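### The only age bands the plan defines omit eligible participants aged exactly 50 and exactly 70, so as written they drop out of the age-group comparisons

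*Protocol article*

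**What the plan says.** **Eligibility.** Textbox 1 admits people from age 50 and sets no upper limit. The abstract's Methods paragraph agrees: "The study’s final sample will include 150 participants (aged ≥50 years". So does the Participants section: "we have recruited 67 (44%) out of 150 participants, all aged ≥50 years and residing in Panama".

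**Bands.** Statistical Analyses plans Student *t* tests between sexes and within age groups, and adds in parentheses that "the sample will be divided in 3 groups: aged 51-59 years, 60-69 years, and >70 years". No other age cut-points appear in the article.

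**Other uses of age groups.**
- Statistical Analyses promises an "in-depth analysis of normative data stratified by age, sex, and education level" and adds that "Test scores will be standardized into *z* scores based on the mean and SD of the respective group".
- Expected Outcomes for Creating Normative Data enters the normalized scores into a "stepwise regression, including sex (male and female), education, and different age groups", without cut-points.
- Dissemination Policy promises each participant a report against peers in the same age range, without defining the ranges.

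**Stated reach of the norms.** The abstract's Results paragraph says: "We plan to generate normative data for Panamanian adults aged >50 years".

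**The concern.** The grouping rule does not cover the population the study enrols. The lowest band starts a year above the entry age, and the middle band ends at 69 while the top band requires more than 70. A fully tested participant aged 50 or 70 has no group.

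Age grouping carries part of the study's purpose: the third objective compares performance across gender and age groups. If the norms use the same bands, a 50- or 70-year-old has no group mean and SD from which to form a *z* score, and a later patient of that age has no stratum to be read against. An analyst who notices the gap must decide where to put these people after data collection has begun, a choice the plan should settle.

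**Working it through.** The plan states no figure for this point, so there is none to reproduce. The check has two parts.

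**1. Coverage of the bands.** Each completed year of age from 50 to 100 was tested against the rule 51 ≤ age ≤ 59, or 60 ≤ age ≤ 69, or age > 70.
- Ages in no band: 50 and 70, and no others.
- With 50-59, 60-69 and ≥70: no age is left out.

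Completed years is the reading that makes most sense of the bands. If ages were fractional, 70.4 would count as more than 70, but people between 59 and 60 or between 69 and 70 would then be unplaced, which is a larger gap.

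**2. How many people this could be.** The inputs are the planned 150, the 67 already assessed, and, for those 67, that they "were on average aged 62.2 (SD 7.6) years". The shape of the distribution is not given, so it is assumed, and the interim figures are carried over to the full sample. With F the assumed distribution function on ages from 50 upward:

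share affected = [F(51) − F(50)] + [F(71) − F(70)]

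| Assumed shape | Share aged 50 | Share aged 70 | Of 150 | Of 67 |
|---|---|---|---|---|
| Gamma starting at 50, mean 62.2, SD 7.6 (shape (12.2/7.6)² = 2.58, scale 7.6²/12.2 = 4.73) | 0.0043 | 0.0200 | 3.6 | 1.6 |
| Normal(62.2, 7.6) cut off at 50 | 0.0170 | 0.0306 | 7.1 | 3.2 |
| Normal cut off at 50, refitted (parameters 59.26 and 9.67) so that the truncated mean and SD are 62.2 and 7.6 | 0.0329 | 0.0253 | 8.7 | 3.9 |
| Even spread over the 31 ages 50 to 80 | 1/31 | 1/31 | 9.7 | 4.3 |

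For example, in the refitted row: (0.0329 + 0.0253) × 150 = 8.7.

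Only the gamma and the refitted normal reproduce the reported mean and SD. Cutting Normal(62.2, 7.6) at 50 moves its mean to about 63.1 and its SD to about 6.8. The even spread has mean 65 and SD about 8.9, and serves as an upper case should later recruitment level out the ages. The range is therefore about 4 to 10 of 150, or 2% to 6%, and about 2 to 4 of the 67 already assessed.

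**The case against.** **It is a slip of wording.** Very probably, with 50-59 and ≥70 intended. But it occurs at two separate boundaries, and the text as it stands is a specific rule that contradicts eligibility. It is not a detail that an article would leave to a fuller document.

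**Age 50 may be left out on purpose.** The abstract's statement that the norms are for people over 50 could be read that way. It conflicts with the entry age given in three other places and does nothing to explain the gap at 70.

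**The bands belong only to the *t* tests.** This stands in part. They are written once, in that sentence. The norming section ranks raw scores without naming bands and then enters age groups without cut-points, and the report section leaves its age range undefined. A reader might infer that 50- and 70-year-olds fall out of every age-group comparison and every norm. The article does not say so. Extending the bands to norms and reports is a likely inference, since no others exist, and no more than that. The multivariable regression uses age without mentioning bands, and the overall sex comparison needs none, so both keep these participants.

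**The oldest band may not be the smallest.** A reader might also infer that the loss at 70 falls on a band already known to be the thinnest. No counts by band are reported, and the abstract expects similar numbers in different age groups. That inference depends on an assumed age distribution.

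**Nothing is lost at data collection.** This is correct. Participants aged 50 and 70 are still enrolled and tested, and the bands can be corrected at any time before analysis. It is the main reason for a modest rating.

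**Conclusion.** Wrong as written. The stated bands leave two eligible ages, 50 and 70, without a group. That conclusion needs only the article's text and ages counted in completed years. The direct consequence is that these participants are missing from the age-group comparisons. Their absence from the age-stratified norms and peer reports is conditional on the same bands being used there.

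The number of people is not known. The range of about 4 to 10 of 150 rests on assumed age distributions and on the interim sample resembling the final one, and no single figure within it should be relied on. With a small share of a descriptive pilot affected, no data lost and a correction that is free, this is a minor to should-fix item. It does not threaten the study.

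**What to change.** 1. In Statistical Analyses, redefine the groups as 50-59, 60-69 and ≥70 years, with age taken in completed years at enrolment.
2. State that the same groups apply to the age-stratified norms, to the age groups in the norming regression and to the age range used in participant reports. If different groups are intended for any of these, give them.
3. In the abstract's Results paragraph, give the norms' age range as ≥50 years, to match eligibility.

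The cost is wording only. Eligibility, recruitment and testing do not change, and the 67 participants already assessed need no further contact. The change is best made before any age-group results are examined.
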